##### Physical and mental health status

Two questions will be administered at the post-intervention assessment to assess physical and mental health status. These questions will ask participants whether they have previously been diagnosed with a chronic physical health condition or a mental health condition by a professional (e.g. a doctor). If there is an existing mental health condition, further questions on the diagnosis and duration of the condition will be asked.

##### Barriers to accessing healthcare services

The Barriers to Access to Care Evaluation Scale (BACE) [30] will be used to assess the severity of the barriers that prevent individuals from accessing healthcare services. This will be measured at the 1-week follow-up assessment. This scale consists of 30 items, categorised into subscales of stigma-related and non-stigma-related barriers associated with the utilisation of mental health services. Each item is rated on a 4-point Likert scale, ranging from 0 (‘Not at all’) to 3 (‘A lot’). The results are reported as the percentage of endorsement for each barrier, with higher scores indicating greater prevalence and impact of these barriers.

#### Process outcomes

##### Patterns of service engagement

We will examine markers of service engagement among men who access one of the four support services. These markers will be derived using data provided directly by the service. Although the nature and extent of data provided by each service will differ slightly, the types of data provided will broadly cover aspects of service use (e.g. number of sessions attended with a psychologist), engagement (i.e. whether an individual completed a course of treatment), and appeal (e.g. consumer-rated usefulness of the service). This data will be provided at an aggregated level across all trial arms. Approaches to analysing this data will depend on the sophistication of data capture across the four services.

### Sample size and power

Based on previous empirical studies of mental health service usage, we estimated that 28% of the participants randomised to one of the three target intervention video messages would click on the link of at least one of the four support services (primary outcome). By contrast, we estimated only 8% of participants randomised to one of the two control video messages would click on the link to at least one support service. Accordingly, we calculated that *n* = 76 participants per trial arm (*N* = 380 total) would provide 80% power to detect our effect of interest with a type I error rate of *α* = 0.05.

### Statistical analysis

#### Analysis of primary outcome

The primary outcome will be analysed using binary logistic regression. These analyses will be conducted using R (version 3.6.3) in R Studio (version 1.2.5033). Models will evaluate the effects of the specific video messaging interventions on help-seeking at post-intervention (i.e. whether the participant clicked on at least one of the four support service links). We will build two models to evaluate specific intervention contrasts:Model 1 will assess differences between the three target video messaging conditions and the two control video messaging conditions by using a single *Intervention* term coded as 1 for the three target interventions and 0 for the two control interventions.Model 2 will assess differences between the three target video messaging conditions by entering two terms: *Video 1* (coded 1 for target video 1 and coded 0 for the other two target videos) and *Video 2* (coded 1 for target video 2 and coded 0 for the other two target videos).

Pending the outcomes of these models, we will perform exploratory analyses to examine differences between specific intervention conditions. As the outcome will be measured at a single time point, no imputation of missing data will be performed. The study sample considered for inclusion will be defined as all participants who meet eligibility criteria and who were randomised to one of the five intervention conditions.

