##### Impact of intervention on participants’ stress

A single stress item from the University of Washington Risk Assessment Protocol (UWRAP) [23] will be used to evaluate the possible adverse effects of the intervention. The UWRAP is a widely used tool for assessing and managing suicide risk. The stress item in the UWRAP is designed to evaluate the level of stress a person is experiencing. The scale ranges from 0 (no stress) to 7 (highest level of stress). The rating is based on an individual’s subjective experience of stress.

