##### Demographics

Demographic variables, including age, current relationship status, highest level of education completed, employment status, and geographic location (i.e. postcode), will be collected at baseline.

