#### Analysis of secondary outcomes

Use of the four services within the 1-week follow-up period will be analysed using the same approach as used for the primary outcome. Help-seeking intentions, which are measured on a 7-point Likert scale, will be measured using ordinal logistic regression. In the case that some levels on this 7-point scale are underrepresented, we will consider combining adjacent categories as appropriate.

We will analyse respondents’ choices made within the DCE by estimating the conditional logit models [31] and mixed logit models [32]. These analyses will be performed using STATA (version 18). These models can be interpreted via the Random Utility Theory which assumes that individuals will choose the alternative that provides them with the highest utility. We will also estimate the Willingness to Pay (WTP), which is the dollar amount individuals are willing to pay for service changes. Relative importance of attributes will also be assessed to understand the relative impact that an attribute has on choice. For example, the preference analysis results will allow us to explore whether men prefer one service type (e.g. peer support) over another (e.g. seeing a psychiatrist). The WTP results will indicate the dollar amount men are willing to pay to receive one service compared to another (e.g. they might be willing to pay $50 more to receive services individually rather than in a group setting). The relative importance results will allow us to understand the ranking of the suicide prevention attributes (e.g. the most important factor affecting choice may be service type, followed by waiting time, cost, etc.). To explore observed heterogeneity, sub-group analyses will be undertaken by interacting the preference weights with a range of socio-demographic characteristics including age, educational attainment, employment status, income levels, etc. This will allow us to understand why individuals in one sub-group (e.g. higher educational attainment) may have different preferences compared to those in another sub-group (e.g. lower educational attainment).

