#### Exploratory analyses

We will also perform exploratory analyses to assess the potential moderating effects of demographic and clinical variables collected, such as participant age and the severity of their suicidal ideation, as well as the length of time participants spent viewing the video message. These analyses will be performed by entering interaction terms into the abovementioned models. Moderators will be assessed one at a time and using separate models.

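### The click and 1-week service-use models carry video terms only, although a stress score and demographics are collected before the video; a short prespecified adjustment would give a modest gain, mainly between target videos

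*Protocol article*

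**What the plan says.** All references are to the protocol article.

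- **Analysis of primary outcome.** Model 1 has one "term coded as 1 for the three target interventions and 0 for the two control interventions". The next sentence reads "Model 2 will assess differences between the three target video messaging conditions by entering two terms", and these are indicators for target videos 1 and 2. No other term is named.
- **Analysis of secondary outcomes.** Service use over the week "will be analysed using the same approach as used for the primary outcome". Intentions "will be measured using ordinal logistic regression", with no terms listed. The discrete choice data have their own choice models, in which "sub-group analyses will be undertaken by interacting the preference weights with a range of socio-demographic characteristics".
- **Exploratory analyses.** Demographic and clinical variables enter the outcome models only as moderators, one at a time: "These analyses will be performed by entering interaction terms into the abovementioned models".
- **What is known before the video.** The Demographics section lists age, relationship status, education, employment and "geographic location (i.e. postcode), will be collected at baseline". Table 1 ticks the UWRAP item at baseline, and its own section gives the 0–7 range. The Assessment schedule places the baseline questionnaires ahead of the video.
- **What is not known before the video.** Table 1 places suicidal ideation (SIDAS), Kessler distress, wellbeing, loneliness and anhedonia at post-intervention only.

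**The concern.** When a baseline variable predicts a binary or ordinal outcome, a logistic model without it estimates a marginal odds ratio. That ratio lies closer to 1 than the conditional one, and the test is usually somewhat less powerful. Here the variables are already in the database, so using them needs no extra data.

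The place where this could matter is the trial's own primary aim, which is to find out which message works best. That rests on Model 2 and on arm-level contrasts of 76 v 76. The 28% v 8% planning assumption separates target from control videos. It says nothing about differences among the target videos.

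Naming the list in advance has a second use. Most of the clinical scales are measured after exposure to the video, so an unplanned later adjustment could easily bring in a post-randomisation variable.

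**Working it through.** **Inputs from the article.** 76 men per arm, 380 in total, equal allocation; click rates 28% (target) and 8% (control); 80% power; α = 0.05. Model 1 therefore compares 3 × 76 = 228 with 2 × 76 = 152. Model 2 uses the 228.

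**Inputs not in the article (assumed).** The prognostic strength of the baseline set, shown as an odds ratio (OR) of 1.0 to 3.0 per SD of one combined score; rates of 18% v 8% for a weaker Model 1 effect; rates of 38/28/18% for the three target videos in Model 2. Tests are taken as two-sided.

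**The plan's own figure.** For one arm against another, with pooled variance under the null:

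n = [1.96·√(2·0.18·0.82) + 0.842·√(0.28·0.72 + 0.08·0.92)]² / 0.20² = (1.065 + 0.442)² / 0.04 ≈ 57 per arm.

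The stated 76 is reached only with an unstated addition such as α/3, 90% power or 25% dropout. That is a separate matter and does not bear on this point.

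**Model 1 at the planned rates, unadjusted.**

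- Expected clickers: 0.28 × 228 + 0.08 × 152 = 63.8 + 12.2 = 76, so the overall rate is 76/380 = 0.20.
- Null SE = √[0.20·0.80·(1/228 + 1/152)] = 0.0419.
- Alternative SE = √[0.2016/228 + 0.0736/152] = 0.0370.
- z = (0.20 − 1.96 × 0.0419)/0.0370 = 3.19, so power is about 99.9%.

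No adjustment can add usable power to this.

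**Effect of adjusting for one standardised score.** Simulated logistic models, 2000 to 3000 runs per setting, with intercepts set to hold the marginal rates. Power is shown as unadjusted → adjusted.

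| OR per SD | Model 1, 28 v 8%: SE of log OR | Model 1, 28 v 8%: variance ratio, standardised risk difference | Model 1, 18 v 8%: power % | Model 2, 38/28/18%: power % |
|---|---|---|---|---|
| 1.0 | 0.342 → 0.343 | 0.999 | 80.8 → 81.0 | 70.4 → 70.3 |
| 1.25 | 0.341 → 0.343 | 0.997 | 81.1 → 82.0 | 70.9 → 71.5 |
| 1.5 | 0.341 → 0.345 | 0.981 | 79.0 → 79.8 | 70.1 → 71.8 |
| 2.0 | 0.341 → 0.354 | 0.938 | 81.1 → 83.3 | 69.7 → 73.8 |
| 3.0 | 0.341 → 0.371 | 0.890 | 80.3 → 85.3 | 69.7 → 78.8 |

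The SE of the log odds ratio rises with adjustment. The estimate moves away from zero faster: at OR 2.0 per SD the mean log odds ratio goes from 1.526 to 1.633. The net gain in squared z at 28% v 8% is about 1%, 2%, 7% and 15% for ORs of 1.25, 1.5, 2.0 and 3.0.

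**Four covariates instead of one score.** Fitting four separate terms with a joint OR of 1.0 to 2.0 gives gains of 0 to 1.4 points (Model 1 at 18% v 8%) and about 0 to 4 points (Model 2 at 38/28/18%). There is no material loss when the covariates are useless.

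**Room for extra terms at the planning rates.** The proposed list costs 3 or 4 parameters if each demographic takes one.

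- Model 2: 0.28 × 228 ≈ 64 clickers. With two video terms that is 64/6 ≈ 11 to 64/5 ≈ 13 clickers per term.
- One target arm v one control arm: 0.28 × 76 + 0.08 × 76 ≈ 27 clickers. With stress alone, 27/2 ≈ 14 per term; with the full list, 27/5 ≈ 5.
- 1-week use: the article gives no rate.

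**The case against.** The strongest reply is that nothing here is an error. An unadjusted logistic model is valid under randomisation, and a covariate list is commonly left to a statistical analysis plan, which is not shown. The single term in Model 1 may only define how the arms are coded. Validity is conceded. On the second part, the article does more than stay silent: it counts the terms in both models, so adding covariates would change a stated specification.

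The next reply is that the gain is small and rests on an unsupported assumption. The baseline set is deliberately minimal, its only clinical scale is one stress item included to detect harm, and the richer scales come too late to use. This stands. It is why the range to rely on stops at an odds ratio of 2.0 and includes zero gain.

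Four stronger readings are tempting, and the article does not support them:

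- A reader might infer that every secondary model has video terms only. The discrete choice models use attribute terms and socio-demographic interactions, and the terms of the ordinal model are not listed.
- A reader might infer that precision on the odds-ratio scale is being thrown away, or that the unadjusted odds ratio is biased. The SE of the log odds ratio does not fall with adjustment, and the marginal and conditional odds ratios are different estimands.
- A reader might infer that the main target-v-control test is weakened. At the planned rates it is not.
- A reader might take the exploratory section as the authors' admission that baseline variables are prognostic. It concerns moderation. Its two participant examples are age, which is the stratifier and a separate question, and ideation severity, which is measured after the video.

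**Conclusion.** The point holds as a modest, inexpensive improvement to a valid plan. Models 1 and 2 and the service-use models are fixed without baseline adjustment although pre-video variables are available.

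The size is nil for Model 1 at 28% v 8%, about 0 to 1.4 points for Model 1 at an assumed 18% v 8%, and about 0 to 4 points for Model 2 at assumed rates of 38/28/18%. The two non-zero ranges assume a joint odds ratio of 1.0 to 2.0 per SD, which the article neither supports nor contradicts. The larger gain at 3.0 per SD should not be counted on. No figure can be given for 1-week use or intentions, because the article states no expected rates for them.

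**What to change.** In Analysis of primary outcome, add to Models 1 and 2 the baseline UWRAP stress score (linear, 0–7) and at most two or three named demographics recorded before the video. Use the same list for 1-week service use and for the ordinal model of intentions. State that scales measured after the video (SIDAS, Kessler distress, wellbeing, loneliness, anhedonia) are not adjustment variables. Report a standardised risk difference beside the adjusted odds ratio for the binary outcomes, and keep the unadjusted models as sensitivity analyses.

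Keep the list short, and cut it to the stress score alone where events are few (Model 2 if clicks are scarce, single-arm contrasts, 1-week use).

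The cost is a sentence or two of text and a few model terms, with no new data. The one real trade-off is that the odds ratio becomes conditional on the covariates, so the effect scale must be named. The list should be fixed before outcomes are examined by arm.

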## Objectives

The primary aim of the Under the Radar trial is to determine which of five promotional messages is most effective at encouraging men with suicidal thoughts, who are ‘under the radar’, to engage with online support services. Five web-based video messages have been developed and will be evaluated in a five-arm randomised controlled trial. Three of the video messages were developed based on themes derived from reviews of the literature [5], a survey of help-seeking in men at risk of suicide [12], and through qualitative interviews with men experiencing suicidal thoughts [15]. Accordingly, these videos reflect the personal experiences and key issues of concern for men who do not access help for their suicidal thoughts. Two control video messages were also created, which provide either generic help-seeking advice or statistics on suicide. We hypothesise that video messages tailored to the concerns and personal experiences of men who are under the radar will be more effective at promoting engagement with support services than either generic help-seeking messaging or to factual data around suicide deaths and attempts.

A secondary aim of this study is to understand what attributes of support services men with suicidal thoughts value most. We will assess these service preferences using the Discrete Choice Experiment (DCE) methodology, which is popular in the field of health economics [16, 17]. DCEs involve presenting individuals with pairs of hypothetical support services that vary on a set of attributes (e.g. cost) and attribute levels (e.g. high cost vs. free). Participants are asked to select which service out of each pair they prefer. Based on participants’ pattern of choices, the relative preferences for the different attributes and levels can be estimated. This methodology will provide us with critical insights into the service attributes that are most appealing to men who are experiencing suicidal thoughts, as well as attributes that may hinder men’s willingness to engage with a service.

Together, the findings from this study are expected to yield valuable insights into how to encourage help-seeking and provide better support for men who are experiencing suicidal thoughts. Additionally, the findings from the trial may serve as the foundation for a nationwide communication campaign aimed at preventing suicide in men and strengthening partnerships with organisations dedicated to suicide prevention.

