### Control conditions: videos portraying generic messages around help-seeking and suicide awareness

The two control video messages portray the following content: (1) one video uses messaging similar to that used on the websites of existing suicide prevention organisations, and promotes help-seeking and general awareness of the availability of support services for individuals experiencing suicidal thoughts; (2) a second video aims to increase the viewers’ general knowledge of the prevalence of suicide in Australia by presenting Australian suicide statistics in the style of a news presenter. These two control video messages are of the same length as the active intervention video messages and are presented in the same style and with the same actor.

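### Model 1 tests the tailored videos only against the average of two unlike controls, so no named contrast tests them against generic help-seeking messaging, as the hypothesis requires

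*Protocol article*

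**What the plan says.** The Objectives section of the Protocol article predicts that the tailored videos will promote engagement better "than either generic help-seeking messaging or to factual data around suicide deaths and attempts". Each of those comparators is one control arm. The section on control conditions says that the first control video "promotes help-seeking and general awareness of the availability of support services", while the second raises knowledge of prevalence by "presenting Australian suicide statistics in the style of a news presenter".

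Under Analysis of primary outcome, Model 1 is a logistic regression with a single intervention term, "coded as 1 for the three target interventions and 0 for the two control interventions". The other model leaves the controls out: "Model 2 will assess differences between the three target video messaging conditions by entering two terms". Beyond these two models the section offers only this: "Pending the outcomes of these models, we will perform exploratory analyses to examine differences between specific intervention conditions".

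The sample size section gives both controls one rate: "we estimated only 8% of participants randomised to one of the two control video messages would click". Under Analysis of secondary outcomes, service use at 1 week "will be analysed using the same approach as used for the primary outcome".

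**The concern.** The hypothesis has two parts, and the named models test neither part separately. Because both controls are coded 0 and allocation is equal, the reference in Model 1 is the mean of the two control click rates. A significant result shows that tailored videos beat that mean. It does not show that they beat generic help-seeking messaging.

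The two controls differ on the dimension that the outcome measures. Control 1 encourages help-seeking and tells men that services exist, and the primary outcome is a click on a service link. Control 2 gives statistics. If control 2 draws few clicks, it can make Model 1 significant when tailored videos are no better than control 1.

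Control 1 is also the comparison that matters most for use. It resembles messaging already found on suicide prevention websites, and the article foresees the tailored videos being used in campaigns. The main result could be read as support for the whole hypothesis when the generic half had no named test. That comparison would probably be run after a significant Model 1, but with exploratory status only.

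**Working it through.** **Inputs.** Sample size section: 28% clicks in target arms, 8% in control arms, 76 men per arm, alpha 0.05 (taken as two-sided; the sidedness is not stated). Random allocation section: 1:1:1:1:1. Model 1 therefore compares 3 × 76 = 228 with 2 × 76 = 152 men. A contrast with one control compares 228 with 76. Control rates other than 8% are assumptions.

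**The plan's own figure.** For 28% v 8% at two-sided 0.05 and 80% power, the pooled-variance two-proportion formula gives 57 per arm, not 76. With 76 v 76, power is 90.2%. The figure of 76 does arise at 80% power with alpha 0.05/3, which the article does not mention. The trial is thus larger than its stated inputs require, and this does not affect the point here.

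**Formula.** With p1 the target rate, p0 the comparator rate, d = p1 − p0, and p̄ the overall rate weighted by group size:

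- SE0 = √[p̄(1 − p̄)(1/n1 + 1/n0)]
- SE1 = √[p1(1 − p1)/n1 + p0(1 − p0)/n0]
- power ≈ Φ[(d − 1.96 × SE0)/SE1], plus a negligible to small opposite tail

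**Model 1 at the protocol's rates.** p0 = (8% + 8%)/2 = 8%, p̄ = 20%, SE0 = 0.0419, SE1 = 0.0370. The bracket is (0.20 − 0.0821)/0.0370 = 3.19, so power is 99.9%.

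**Model 1 when tailored videos have no advantage over control 1.** Set target and control 1 both at 28% and vary control 2. For control 2 at 8%, p0 = (28% + 8%)/2 = 18%, p̄ = 24%, SE0 = 0.0447, SE1 = 0.0431. The bracket is (0.10 − 0.0877)/0.0431 = 0.29, so power is 61%.

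The last column requires tailored v control 1 and tailored v control 2 both to be significant in favour of tailored. It comes from 400,000 simulated trials with the logistic Wald test.

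| Control 2 | Pooled control | Model 1 significant (formula) | Model 1 favours target (simulation) | Both direct contrasts favour target (simulation) |
|---|---|---|---|---|
| 8% | 18% | 61% | 61% | 2.2% |
| 13% | 20.5% | 38% | 37% | 2.0% |
| 18% | 23% | 19% | 18% | 1.4% |
| 23% | 25.5% | 8% | 7% | 0.6% |

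**Power of the direct contrasts.** Target at 28%, 228 v 76 men. For control 1 at 8%, p̄ = 23%, SE0 = 0.0557, SE1 = 0.0430. The bracket is (0.20 − 0.1093)/0.0430 = 2.11, so power is 98%.

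| Control 1 | Target v control 1 (formula) | Both contrasts, control 2 at 8% (simulation) |
|---|---|---|
| 8% | 98% | 96% |
| 13% | 79% | 77% |
| 18% | 40% | 40% (0.395) |

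With control 1 at 18% and control 2 at 8%, Model 1 is significant in 95% of simulated trials, while the contrast with control 1 has 40% power. Model 1 can look decisive while the evidence against generic messaging stays uncertain.

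**The case against.** The best defence reads the hypothesis as one class of video against another. The design has three active and two control arms, one heading groups the controls, and the sample size section gives them a single rate. Model 1 tests exactly that contrast. The exploratory provision already allows arm-level comparisons, and an analysis plan that is not shown may name them. The wording of the Objectives still refers to either comparator, which most naturally means each. The article also does more than leave detail open: it fixes the primary contrasts and makes every other comparison exploratory and dependent on the model results.

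A second defence stands in full. In the table of false support, tailored videos really do beat the average control, so the 61% is not a type I error of Model 1. It becomes an error only if the result is reported as superiority over generic messaging, and the article does not say that it will be. The 61% also needs control 1 to equal the tailored videos and a 20-point gap between two controls that share actor, length, style and service directory. It is an assumed extreme, not an expected rate. The small percentages for the two-contrast rule follow largely by construction, because the contrast with control 1 has a one-sided error of at most about 2.5%.

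A third point also stands: the protocol gives no rates for service use at 1 week, so power for the same contrasts on that outcome cannot be stated.

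**Conclusion.** The concern holds. The named models do not test whether tailored videos beat generic help-seeking messaging, although the Objectives hypothesise it. Model 1 is a valid test of a different question, superiority over the average control.

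The size of the problem depends on how far the control rates differ. At a common 8% there is none. If control 1 matches the tailored videos at 28%, the chance that Model 1 is significant with no advantage over generic messaging runs from 8% to 61% as control 2 falls from 23% to 8%. These figures rest on assumed control rates and a two-sided 5% test. The point should be addressed, but it does not invalidate the primary test.

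**What to change.** 1. Keep Model 1 as the primary test, and state its conclusion as superiority over the average of the two controls.
2. Before unblinding, prespecify two named contrasts, the three target videos v control 1 and the three target videos v control 2, to be run whatever Model 1 shows.
3. Claim the full hypothesis only if both contrasts favour the target videos at two-sided 5%. No alpha split is needed, because both must hold.
4. Use the same wording and contrasts for service use at 1 week, noting that their power there is unknown.

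The cost is two contrasts and one reporting rule. The primary test does not change after recruitment began, and at the protocol's click rates no extra men are needed. The drawback is that the full hypothesis may go unsupported if control 1 performs better than planned, given the loss of power shown above for control 1 at 13% and 18%.
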